### Randomization and sampling procedures

Among the 16 districts in East Gojjam zone, Debre-Markos, Gozamin and Machakel were selected on purpose after confirming that each of them did not have any current projects aiming to increase the utilization of maternal health services. Health posts (with their catchment areas) under selected districts are the unit of randomization for this trial. Since a component of the planned intervention will be delivered at the community level, individual randomization is not appropriate in this situation as it would result in contamination. Thus, 30 nonadjacent health posts (clusters) were selected. Once cluster recruitment has been completed, participating clusters were allocated to one of the two trial arms (at 1:1 allocation) on an equal basis (a total of 30 clusters, fifteen clusters in each arm) using an SPSS-generated random number sequence. This trial aims to increase service utilization, and we used mothers who had previously delivered as a baseline to compare the status of service utilization in selected areas, as well as to compare the status of maternal health service utilization after the intervention. For this, all mothers who have given birth in the previous 1 year, regardless of their place of delivery, who are living in the catchment area of the selected health posts were entered in SPSS and ‘random case selection’ of the required sample size was performed.

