### Participant eligibility criteria

The participants for this trial will be pregnant mothers residing in three of the selected districts of East Gojjam zone (Debre-Markos, Gozamin and Machakel districts). Recruitment will pass a two-stage screening process. Using a preset criterion, the initial screening will be done at the community level using the pregnancy screening checklist from Stanback et al [18]. (last menstrual period for gestational age dating), and mothers having a suspected pregnancy will have a laboratory confirmation at the health center. Those having a gestational age of 16 weeks will be recruited for the study. Mothers who fulfill the above criteria but who have severe psychological illness which could interfere with consent and study participation, those who have severe clinical complications that need hospitalization and mothers who need a special type of ANC follow-up, other than the recommended focused ANC, will be excluded from the study.

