### Sample size determination

The sample size was calculated based on the recommendations of sample size calculations for cluster randomized controlled trials with fixed number of clusters [19] by using the following assumptions: utilization of the third PNC in the control group is 16% based on a previous study [20], the number of clusters available is 30 (15 clusters per arm), with 95% confidence interval and 80% power, and an intracluster correlation coefficient of 0.04849 [21]. The sample size was calculated to determine the number of observations required per cluster for a two-sample comparison of proportions (using normal approximation) using STATA software. Assuming individual randomization, the sample size per arm is 194; allowing for cluster randomization, the average cluster size required is 40. A total of 1200 pregnant mothers (600 in the intervention and 600 in the control groups) will be recruited to detect a 12% increase in the utilization of ANC visit four, skilled birth attendance and PNC. The outcome is treated as a binary measure.

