### Analysis plan

Data from the trial will be analyzed by an intention-to-treat analysis at both cluster and participant levels. Participants will be assigned to the cluster they were resident in at the time the trial began. The primary data analysis will take place at the cluster level. Risk ratios will be computed at the cluster level, and the results of this cluster summary will be compared using *t* tests. Primary and secondary outcomes will be compared between intervention and control groups with random effects logistic regression models, taking account of clustering/correlation. All estimates will be presented with 95% confidence intervals. STATA version 13.0 will be used to run the analysis.

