## Trial status

Thirty clusters have been selected and the preparatory activities such as development of training manuals, referral slips and registers are completed. A sensitization workshop for local health administrators and training for intervention implementers (HEWs and midwives) has been conducted. The specification for specially designed boxes for health posts and health centers has been developed and procurement and distribution has been made accordingly. The baseline study has collected data in both the intervention and control clusters, and enrollment of mothers as per the criterion is being conducted. This is protocol version 1, dated 26 March 2019. Recruitment began on 22 November 2018, and the approximate date of recruitment completion is October 2019.

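### Baseline utilization was collected in both arms, but the stated primary t test on cluster summaries uses neither it nor district, so precision is given up (without bias)

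*Protocol article*

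**What the plan says.** All places are in the protocol article.

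- **Randomization and sampling procedures.** Thirty non-adjacent health posts were allocated 15:15 from an SPSS random number sequence; stratification or matching is not mentioned. The baseline is a random sample of women in the posts' catchments who gave birth in the preceding year, wherever they delivered. It has two stated uses. The first is a description of the areas: "we used mothers who had previously delivered as a baseline to compare the status of service utilization in selected areas". The second is a comparison with utilization once the intervention has been delivered.
- **Trial status.** "The baseline study has collected data in both the intervention and control clusters".
- **Participant eligibility criteria.** Participants come from "three of the selected districts of East Gojjam zone (Debre-Markos, Gozamin and Machakel districts").
- **Screening and enrollment.** A woman is recruited on a positive urine HCG test at the health center and has her first ANC visit that day.
- **Analysis plan.** "The primary data analysis will take place at the cluster level". Cluster-level risk ratios are computed and the summaries compared by t tests. Random effects logistic regression that allows for clustering is also planned. No covariate is named for either analysis.
- **Sample size determination.** The inputs are "utilization of the third PNC in the control group is 16"%, "the number of clusters available is 30 (15 clusters per arm"), and "with 95% confidence interval and 80% power, and an intracluster correlation coefficient of 0.04849". The 1200 women are "to detect a 12% increase in the utilization of ANC visit four, skilled birth attendance and PNC".

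**The concern.** With 15 clusters per arm, the arms can differ by chance in prior utilization. A post's past rate for an outcome is usually among the best predictors of its future rate, and here it has already been measured. A primary test that leaves it out carries between-post variation that could have been removed. This matters most for the fourth ANC visit and facility delivery, where the planned size gives less than 80% power on the article's regional rates.

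The second stated use of the baseline raises a different problem. Baseline women are recent mothers with or without antenatal care, whereas enrolled women have by construction made a first ANC visit. A before-after difference between these groups mixes any effect with a change in who is counted.

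**Working it through.** **Inputs from the article.** Control rate 16% and a 12-point increase; ICC ρ = 0.04849; k = 15 clusters per arm; m = 40 women per cluster. Regional rates (Setting): first ANC 67.1%, fourth ANC 31.5%, facility delivery 27.1%.

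**Assumptions not in the article.** Two-sided α of 0.05 (read from the 95% interval); the same ICC for every outcome and for the baseline; 40 baseline women per cluster; a cluster autocorrelation (CAC), meaning the correlation between a post's true rates in the two periods, varied from 0 to 0.9. Calculations are on the difference scale.

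**The plan's own figure.** The stated 194 per arm and 40 per cluster do not reproduce exactly. The pooled normal formula gives 186, and the fixed-cluster formula 194(1 − ρ)/(15 − 194ρ) gives 33.0. That is a separate matter; the planned 40 is used below.

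**Step 1: unadjusted t test.** Design effect = 1 + 39 × 0.04849 = 2.891. SE² = [p₁(1 − p₁) + p₂(1 − p₂)] × 2.891/(40 × 15). Power is from the noncentral t with 28 df.
- 16% v 28%: (0.1344 + 0.2016) × 2.891/600, SE 0.0402, power 82.1%.
- Fourth ANC 31.5% v 43.5%: (0.2158 + 0.2458) × 2.891/600, SE 0.0472, power 69.0%.
- Delivery 27.1% v 39.1%: (0.1976 + 0.2381) × 2.891/600, SE 0.0458, power 71.5%.

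**Step 2: gain from the baseline.** Reliability of a cluster mean is R = 40 × 0.04849/2.891 = 0.671. The correlation of baseline and end-line cluster rates is r = CAC × R, and the variance is multiplied by 1 − r². Arm, baseline proportion and two district terms leave 30 − 1 − 1 − 1 − 2 = 25 df. District is charged its degrees of freedom but given no explanatory credit.

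| CAC | r | 1 − r² | Fourth ANC power | Delivery power |
|---|---|---|---|---|
| Unadjusted, 28 df | – | 1 | 69.0% | 71.5% |
| 0 | 0 | 1 | 68.7% | 71.1% |
| 0.3 | 0.20 | 0.959 | 70.4% | 72.9% |
| 0.5 | 0.34 | 0.887 | 73.8% | 76.2% |
| 0.9 | 0.60 | 0.635 | 86.6% | 88.4% |

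The SE falls by 1 − √0.887 = 6% at CAC 0.5 and by 1 − √0.635 = 20% at CAC 0.9.

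**Step 3: a smaller baseline sample.** With 20 baseline women per cluster, baseline reliability is 20 × 0.04849/(1 + 19 × 0.04849) = 0.505, and r = CAC × √(0.671 × 0.505). This gives r = 0.29 at CAC 0.5 and 0.52 at CAC 0.9, with fourth-ANC power of about 72% and 82% (25 df).

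**Step 4: before-after comparison.** Fourth-visit attenders are also first-visit attenders, so among women with a first visit the regional fourth-visit rate is 31.5/67.1 = 46.9%. Against 31.5% in all mothers, the difference is 46.9 − 31.5 = 15.4 points with no intervention effect, which is larger than the 12-point target.

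**The case against.** The strongest reply is that nothing here is an error. The article does not say that its analyses are unadjusted: the logistic model could carry baseline and district, a cluster-level t test can be run on covariate-adjusted residuals, and covariate lists are often left to an analysis plan, which is not at hand. Randomisation keeps the t test valid, chance imbalance is already allowed for in its error rate, and the outcome used for sizing has 82% power. The gain depends on two quantities that the article does not give, and it is close to nil if posts' rates are weakly correlated over time. The difference between baseline and enrolled women may itself lower that correlation.

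Most of this stands, and it limits the point to efficiency. It does not remove it: the article does fix the primary method as a t test on cluster summaries, and a better method is available with data already in hand.

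Four stronger readings are tempting but not supported:
- A reader might infer that the baseline serves only a before-after comparison. The article also uses it to compare the selected areas.
- A reader might infer that the before-after change is the trial's test of effect. The Analysis plan compares intervention with control, and baseline data exist in both arms, so a population shift common to both arms would not by itself create an arm difference.
- A reader might label the districts urban or rural. The article speaks of both settings and calls Debre-markos a city, but labels no district.
- A reader might take the 15 points as certain. They rest on regional survey rates and on the enrolment rule. First ANC attendance is also listed as a secondary outcome, which could not vary among women enrolled at that visit, so the end-line population is not fully settled.

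**Conclusion.** The point holds as a low-cost improvement in precision, together with a caution on interpretation. It is not a finding of bias or invalidity. The planned t test is valid and has about 82% power for 16% versus 28%.

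For the other two outcomes, with 40 baseline women per cluster and ICC 0.04849, adjustment ranges from a loss of about 0.3 to 0.4 of a point (autocorrelation 0) to a gain of about 17 to 18 points (autocorrelation 0.9). At 0.3 the gain is only 1 to 2 points, and at 0.5 about 5. The documents do not show where in that range this trial lies, but the downside is negligible.

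The before-after comparison is a stated use of the baseline between groups that differ by construction. On the regional rates it could show about 15 points for the fourth ANC visit with no effect.

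**What to change.** 1. Make the primary cluster-level analysis a linear model of each post's end-line proportion on arm, the same post's baseline proportion for the same outcome, and district. Apply it to each primary outcome that has a baseline counterpart.
2. Put the same cluster-level covariates in the random effects logistic model.
3. State that the baseline serves to describe the areas and as a cluster covariate, and that a raw change from baseline to end-line will not be interpreted as an intervention effect. That the baseline women are different women does not prevent this use: an earlier cohort's rate is a legitimate cluster-level covariate.

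The cost is two or three sentences in the analysis plan, ideally fixed before end-line data are seen, and three degrees of freedom (25 instead of 28). No new data are needed. If the baseline turns out to be uninformative, the loss is about 0.3 to 0.4 of a percentage point of power.

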### Screening and enrollment

In Ethiopia, the linkage between primary health care units is defined and each health post has its own catchment population to serve. This linkage works primarily by proximity of health facilities to the catchment population. Community-level referral of this trial works following this defined primary health care unit linkage. Based on this, HEWs will use a family folder (a detailed record about households) to identify women of reproductive age. The first-level screening will then take place at the community level using the pregnancy screening checklist of Stanback et al. [18]. Mothers having suspected pregnancy will receive a community-level referral slip for them to be received by the nearby health center. The second screening will take place at the health center using a beta-human chorionic gonadotropin (HCG) urine test as laboratory confirmation of pregnancy. Mothers who have known pregnancy but have not initiated the first ANC will also be referred for the service. If a mother has a positive HCG result, she will be recruited for the study and on the same day she will receive the first ANC service.

### Intervention description

#### Intervention

The intervention has two main focuses; first, creating demand at the community level performed by HEWs and, second, service utilization monitoring through dropout-tracing mechanisms. Two separately designed boxes were introduced to help facilitate the above interventions. Health posts received ‘health education scheduling boxes’. The main purpose of these 12-compartment boxes (Fig. 2) is to prioritize the most common reasons raised by mothers for not utilizing each of the maternal health services and to provide focused health education. As the Ethiopian health system encourages mothers to receive maternal health services at the health-center level and above, for these interventions HEWs have performed more demand-creation activities.

##### Health post

HEWs use family folders to locate women of reproductive age and carry out home-to-home pregnancy screening using the checklist of Stanback et al. [18]. Mothers having a suspected pregnancy will be referred to the nearby health center for laboratory confirmation and, if they are pregnant, they will receive the first ANC at the receiving health center. In this process, HEWs link mothers with the receiving health center through a referral slip.

**Fig. 2 Fig2:**
[figure not shown]
Representation of the 12-compartment health education scheduling box to be presented at the health post (C compartment). For example, if a mother misses antenatal care (ANC) following a knowledge gap, the reason-picking card will be placed in compartment 4. Compartments containing more cards will be a focus for future discussion. PNC, postnatal care

While conducting home-to-home visits, HEWs identify reasons raised by women for not utilizing maternal health services (ANC, skilled birth attendance and PNC) and the list of reasons will be kept in health education scheduling boxes. Reasons raised by most mothers will be the topic for health education by HEWs. If a service is missed, HEWs will be informed and they will identify the reason with the mother and discuss it with her in attempt to get her to resume the service.

##### Health center

Once the mothers are linked to a nearby health center, they will be followed for their subsequent attendance of consecutive maternal health care services of ANC (second to fourth visits), skilled birth attendance, and PNC (1–3 visits). This will be checked using a specially designed service utilization monitoring box. This box is a nine-compartment box (Fig. 3); the first compartment is for mothers suspected of being pregnancy using the pregnancy screening checklist from the HEWs. If the mothers arrive and confirm their pregnancy (via HCG test) they will receive the first ANC and their card will be transferred to the next compartment; the same procedure will be followed for the coming consecutive maternal health care service visits. The visits for ANC will follow the four-visit WHO ANC model (i.e., first ANC before 16 weeks of gestation, second ANC at 24–28 weeks, third ANC at 30–32 weeks, fourth ANC at 36–40 weeks); facility delivery is that assisted by skilled health-care providers at the health-center level and above; and visits for PNC are PNC visit 1 at 6 h, PNC visit 2 at 6 days and PNC visit 3 at 6 weeks after delivery. This service utilization monitoring box will help midwives identify mothers who fail to follow the above smooth transition. If a mother is identified as a ‘dropout’, midwives at health centers will communicate to HEWs in the area in which the mother lives. Again, these mothers will be approached for person-centered health education to resume their service within the recommended time interval.

**Fig. 3 Fig3:**

Representation of the service utilization monitoring box at the health center. The individual folder for the mother with a list of services completed for that specific visit will be placed in the correct compartment; when the mother attends for a subsequent service her folder will be transferred to the next compartment, but when a mother does not attend her folder will remain in the previous compartment. Using this process, the dropouts for each visit can be traced. ANC antenatal care, PNC postnatal care

#### Control

Participants in the control arm will receive existing routine care of mass health education by HEWs and will receive maternal health care services at health centers through being given appointments for subsequent follow-ups. Unlike the intervention arm, this group will not receive community-level pregnancy screening and will not be given access to a health education scheduling box, a person-centered health education manual or a service utilization monitoring box.

### Intervention process

Before the study team introduced the intervention, a detail intervention package was developed with a focus on narrating what steps to follow while implementing the intervention. In addition, other pre-introduction activities were undertaken, including development of a training manual and a person-centered manual for HEWs and health care providers (Amharic version), development of the specification for the health education scheduling boxes and service utilization monitoring boxes, and procurement of 15 boxes for the health posts and 5 boxes for the health centers. A sensitization workshop was conducted for local health administrators, along with training for all HEWs from 15 selected health posts and the training of 2 midwives from each selected health center (one delivery case team lead and one midwife). Boxes, printed checklist referral slips, registers and manuals were distributed accordingly, and onsite orientation was made. The community survey and enrollment was then started. Follow-up visits were made based on the previously developed compliance parameters.

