### The context of the primary health care unit

The Ethiopian health service is structured into a three-tier system, with primary, secondary and tertiary levels of care. The primary level of care includes primary hospitals, health centers and health posts. The primary health care unit is composed of a health center and five satellite health posts. These provide both preventive and curative services to approximately 25,000 people altogether. Health centers serve as a referral center and practical training institution for health extension workers (HEWs). In turn, primary hospitals serve as a referral center for health centers under its catchment areas and a practical training center for nurses and other paramedic health professionals [17].

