Ethiopia’s health-extension program is a community-based strategy to deliver health promotion, disease prevention and selected curative health services at the community level. It is a mechanism to provide health services free of charge to all segments of the population in the country by paid HEWs. HEWs are drawn from the community they are going to serve, and are trained for 1 year. Two HEWs per health post are deployed to provide services under the 16 packages by making house-to-house visits. Improving access and utilization of latrines, increasing contraceptive acceptance rates and ANC and PNC, improving health-seeking behavior, expanding vaccination services, improving malaria control and prevention, and reduction of new human immunodeficiency virus infection are some of the major packages that are expected to be delivered by HEWs. HEWs spend 75% of their time on home-to-home visits providing promotional and preventive interventions and 25% of their time at health posts [13, 17]. Even though maternal health services are delivered at different levels of the health system, this trial is focused on improving service delivery in the primary health care units. Using the existing referral linkages between primary health care units, all three contact points (ANC, delivery and PNC) are expected to happen at the health center level (as recommended) where the monitoring box is placed. If the mother made one of the visits, including delivery by her preference, at facilities other than the intervention health center it will be tracked by HEWs and, if it is confirmed, her individual folder will be transferred to the next stage. However, if the mother is permanently moved to another facility/residence, she will be excluded from the study. Since the services are similar for primary hospitals and above, the trial can also be applied to hospitals.

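### Health posts are randomised and analysed, but the monitoring box and trained midwives sit at 5 health centres, and neither the sample size nor the primary t test has a health-centre level

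*Protocol article*

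**What the plan says.** **Randomised unit.** Under Randomization and sampling procedures: "Health posts (with their catchment areas) under selected districts are the unit of randomization for this trial". Allocation is 1:1 from a random number sequence, giving "a total of 30 clusters, fifteen clusters in each arm". No restriction by health centre is described. The stated protection against contamination is distance between posts: "Thus, 30 nonadjacent health posts (clusters) were selected".

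**Level of delivery.** Under The context of the primary health care unit: "The primary health care unit is composed of a health center and five satellite health posts". The same section says "all three contact points (ANC, delivery and PNC) are expected to happen at the health center level", but it also lets a woman use another facility, in which case the visit is followed up and counted. Under Intervention process the trial reports "procurement of 15 boxes for the health posts and 5 boxes for the health centers" and "the training of 2 midwives from each selected health center (one delivery case team lead and one midwife".

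**Control arm.** Under Control, these women also receive their maternal care at health centres. The article does not say whether those are the box centres or others. They are to have no access to either box or to the person-centred manual, and no community pregnancy screening.

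**Sample size and analysis.** The calculation uses one ICC (0.04849) and "the number of clusters available is 30 (15 clusters per arm". The Analysis plan makes the cluster-level comparison primary, by t test. It adds a random-effects logistic model without naming the level of the random effect.

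**The concern.** One of the intervention's two components, the tracing of dropouts, runs from the health centre. The primary outcomes are visits that are expected to take place there. Fifteen intervention posts over 5 centres is about three posts to a box and a pair of trained midwives. The design, power and primary test treat each post as a separate, independent unit.

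There are two pure cases, and mixtures of them:

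- **Separate centres.** Control posts refer to other centres. Every centre then belongs to one arm, centre quality and access are confounded with arm, and posts under one centre are correlated. A 28-df t test on posts would give intervals that are too narrow.
- **Shared centres.** Some control posts refer to box centres. Trained midwives, and any change in centre practice, then reach control women, and the contrast may shrink. Non-adjacency does not prevent this, because two posts that do not touch can be satellites of one centre.

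The plan provides for neither case.

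**Working it through.** **Inputs from the article.** Control proportion 0.16; a 12% increase, read as 12 points, so 0.28; 5% level (two-sided assumed); 80% power; ICC 0.04849; 15 posts per arm; 40 women per post; 5 centre boxes for 15 intervention posts.

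**Assumptions, because the article gives no figure.** 5 control centres; 3 study posts per centre in both arms; a share f of the ICC lying at centre level, so that women in different posts under one centre have correlation ρ = f × 0.04849.

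**1. The plan's own figures.**
- Unpooled variance: 0.16×0.84 + 0.28×0.72 = 0.336. With a t(28) critical value, n = 0.336 × (2.048 + 0.842)² / 0.12² ≈ 194.9, against the stated 194.
- Fixed-cluster formula m = n(1 − ICC)/(k − n×ICC), with n = 194: 33.0 at k = 15 and 40.2 at k = 14. The stated 40 is reproduced if one cluster per arm is given up as a small-sample allowance.
- Power as planned: design effect 1 + 39×0.04849 = 2.89; effective n = 600/2.89 = 207.5 per arm; SE = √(0.336/207.5) = 0.0402; 0.12/0.0402 = 2.98; noncentral t with 28 df gives 82%.

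**2. Separate centres.**
- Design effect = 1 + 39×0.04849 + 80ρ, where 80 is the number of women in the two other posts under the same centre. A valid test on 5 v 5 centre summaries has 8 df.
- Type I error of the post-level t test: in units of p(1 − p), a post mean has variance V = 2.891/40 = 0.0723. The true variance of the arm contrast exceeds the estimated one by (V + 2ρ)/(V − 2ρ/14). The 28-df critical value is divided by the square root of this ratio.

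| f | ρ | Design effect | Effective n per arm | Power, 8 df | Variance ratio | Type I error, post-level test |
|---|---|---|---|---|---|---|
| 0 | 0 | 2.89 | 207.5 | 74% | 1.00 | 5% |
| 25% | 0.0121 | 3.86 | 155.4 | 62% | 1.37 | 9% |
| 50% | 0.0242 | 4.83 | 124.2 | 53% | 1.75 | 13% |
| 100% | 0.0485 | 6.77 | 88.6 | 40% | 2.59 | 21% |

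Simulated null trials with this layout gave type I errors of about 9%, 13–14% and 22% in the last three rows. The centre-level test stayed at 5%.

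**3. Posts randomised one by one, whatever their centre.** When the same simulated posts were allocated to arms at random, the post-level t test rejected in about 5% of null trials at all three values of f. Random allocation of posts protects the size of the test.

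**4. Shared centres: dilution.** Suppose a share of the 12-point effect reaches controls, with effective n 207.5 and 28 df. Leakage of 10% (17.2% v 28%) gives 73% power, 20% (18.4% v 28%) gives 61%, and 25% (19% v 28%) gives 56%. The article supports no particular share.

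**5. Which case?**
- If the 30 posts lay three to a centre in 10 centres, C(10,5) = 252 of C(30,15) = 155,117,520 allocations would leave every centre in one arm. Complete separation would therefore not be expected from unrestricted allocation by post.
- The context section refers to a woman's health centre as an intervention one, which hints at separation.
- With five satellite posts per centre, 5 box centres cover 25 posts, leaving room for 10 control posts, so at least 5 of the 15 control posts would refer elsewhere. A mixture is possible.

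**The case against.** The strongest reply is that the inflated error rates belong only to the separate-centre case, which the stated allocation makes improbable. That is right as far as it goes. If posts were randomised individually as described, the t test holds its size, as step 3 shows. A reader might infer that the trial's false-positive rate is inflated or that the primary test is invalid. The article does not support that without evidence that the arms use different centres.

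A reader might equally infer that controls are contaminated. That also goes too far. Controls have no box access, so no folder in the monitoring box. Tracing runs back through the health extension workers of the woman's own area, and only those of the 15 intervention posts were trained. What remains is the behaviour of the trained midwives and general centre practice. Dilution also costs power and biases towards no effect; it does not invalidate the test.

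Nor do all outcome visits take place at the 5 box centres: visits elsewhere count, delivery at higher-level facilities qualifies, and data come from interviews at home.

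Two further points stand. The random-effects model could carry a centre level in an analysis plan not shown. And the drop from 82% to 74% at f = 0 is only the price of 8 rather than 28 df.

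What the reply does not remove is that the single ICC, the 15-per-arm power basis and the primary cluster-level t test are fixed in the article, and that none of them allows for a shared centre.

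**Conclusion.** The point holds as a conditional one. The article fixes the post as the unit of randomisation, power and primary analysis, while a main component and the expected outcome visits sit at a centre level that the plan does not handle.

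- If the arms use separate centres, the planned test has type I error of about 9–10%, 13% and 22% when 25%, 50% or 100% of the ICC is at centre level. A valid test then has 62%, 53% and 40% power.
- If centres are shared and allocation was as described, the test is sound. The loss is possible dilution through midwives and centre practice, limited by the withholding of box, folder and trained extension workers. The 56% power at 25% leakage is an illustration, not an estimate.

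These sizes rest on 5 control centres, three posts per centre and assumed values for the centre share and the leakage. Which case applies, or what mixture, cannot be settled from the article.

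**What to change.** Screening and enrollment says that the linkage between posts and health centres is already defined. Use it to state which centre serves each of the 30 posts, by arm. Then:

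- **Separate centres:** make health centre the top level of the primary analysis, either by centre summaries with df = centres − 2, or by a centre random effect above post with a small-sample correction.
- **Shared centres:** stratify the cluster-level analysis and the model by centre, report how many control women attend box centres, and state that the effect may be diluted.
- **Mixed:** account for both.

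Restate the power for whichever design results. The change needs analysis wording and a map that exists, with no new data collection. The cost is fewer degrees of freedom and a less favourable power figure.
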